### Secondary outcomes

A detailed list of secondary outcomes with definitions has already been published and is outlined in Additional file 1: Table S4. These secondary outcomes can be grouped as follows:***Secondary outcomes related to incident proximal lower-extremity DVT*****.** These outcomes test the secondary hypotheses that IPC reduces the extent of incident proximal lower-extremity DVT and reduces central-venous-catheter- and non-central-venous-catheter-related incident proximal lower-extremity DVT
*Unilateral incident proximal lower-extremity DVT*

*Bilateral incident proximal lower-extremity DVT*
*Number of veins with DVT.* As per our protocol, the venous system is examined by documenting compressibility at the following six sites: common femoral, proximal superficial femoral, mid superficial femoral, distal superficial femoral, popliteal veins and trifurcation [5]. We will document the number of veins involved as a measure of DVT extent
*Complete occlusion (with one vein at least non-compressible)*

*Incomplete occlusion (with all veins at least partially compressible)*
*Central-venous-catheter-related incident proximal lower-extremity DVT* as defined previously [5]
*Non-central-venous-catheter-related incident proximal lower-extremity DVT*
2.
***Secondary outcomes related to lower-extremity DVT other than incident proximal lower-extremity DVT***
*Prevalent – proximal DVT.* DVT diagnosed on the first ultrasonography within the first three calendar study days are considered “prevalent,” (i.e. reflecting a baseline characteristic); however, some of these DVTs may have occurred after enrollment. While a narrower time window to perform the first ultrasonography would have been ideal, feasibility considerations (i.e. logistics of performing an ultrasonography by a certified technician) mandated a broader time window. Therefore, it is possible that the intervention may reduce prevalent proximal DVT*Distal DVT (incident + prevalent).* In general, we will not consider isolated distal lower-extremity DVT. Study surveillance ultrasonography does not include distal calf veins (i.e., peroneal, posterior, anterior tibial, and muscular veins). However, if diagnosed by the treating team, then we will document their occurrence. If lower-extremity DVT occurs in both proximal and distal veins, it will be counted as a proximal DVT
*All lower-extremity DVT (all proximal and distal)*
3.

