***Secondary outcomes related to PE***

*Incidence of PE*

*Extent of PE: unilateral, bilateral*
*PE with cardiopulmonary complications* (supraventricular arrhythmias, ventricular arrhythmias, hypotension (systolic blood pressure ≤ 80 mmHg or decrease of 30 mmHg from baseline) or increase in inotropic support ≥ 50% from pre-event, endotracheal intubation, cardiopulmonary arrest, pulmonary artery hypertension (pulmonary artery (PA) systolic ≥ 60 mmHg or death)
*Composite all lower-extremity DVT and PE*
4.

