***Mortality outcomes assessed at ICU discharge, 28 days, hospital discharge and 90 days***
11.***Composite outcome of lower-extremity DVT, PE and 28-day mortality***
**to** address the competing risk of VTE and mortality [12, 13]12.Serial respiratory, cardiovascular Sequential Organ Failure Assessment (SOFA) scores13.Serial daily fluid intake, output and balance and vasopressor doses

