#### Analysis of secondary outcomes

Secondary outcomes will be compared in the intention-to-treat cohort only using a chi-square test. Results will be reported using RR and 95% CI.

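### Distal DVT has no scheduled ascertainment but is compared between arms and counted in all-DVT and at least one VTE composite, so those RRs depend on calf imaging being similar in both arms

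*Protocol article*

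**What the plan says.** Under Secondary outcomes (item 1), the article lists six examined sites, from the common femoral vein to the trifurcation. Item 2 adds: "Study surveillance ultrasonography does not include distal calf veins". It also says: "In general, we will not consider isolated distal lower-extremity DVT". The exception follows directly: "However, if diagnosed by the treating team, then we will document their occurrence".

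That text sits under the listed secondary outcome "Distal DVT (incident + prevalent" and is followed by a second outcome, "All lower-extremity DVT (all proximal and distal". Item 3 carries the wider set forward: "Composite all lower-extremity DVT and PE". Item 11 is a "Composite outcome of lower-extremity DVT, PE and 28-day mortality", with no restriction to proximal DVT.

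On analysis: "Secondary outcomes will be compared in the intention-to-treat cohort only using a chi-square test". Results are given as RR with 95% CI.

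The Abstract says that radiologists reading leg ultrasonography are blinded and that patients and the treating team are not. Under Diagnostic testing, the number of VTE tests is compared between groups because the study is open-label. For the legs, this covers whether a patient had any ultrasonography, the time to the first, and the number per patient.

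**The concern.** For proximal DVT, every patient is due a baseline scan and twice-weekly scans, read by blinded radiologists. For isolated distal DVT nothing is scheduled. A patient whose calf was never imaged enters the intention-to-treat comparison as free of distal DVT, and the decision to image rests with staff who know the allocation. Blinded reading protects how a scan is interpreted, not whether it is ordered.

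If the two arms are imaged at different rates, part of any difference in distal DVT comes from imaging. That part is carried into all-DVT and the DVT-plus-PE composite, which readers of a VTE-prevention trial will look at closely. The item is also internally inconsistent: it sets isolated distal DVT aside in general, yet names it as one outcome and counts it in another.

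**Working it through.** **The plan's own figures.** The documents give no rate for distal DVT or for calf imaging. The only planning figure is for the primary outcome (7% v 4%, 80% power, 2000 patients). It reproduces: the total is 1942 with a continuity correction, and 1000 per arm gives about 84% power without one. It does not bear on this point.

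**Inputs, all assumed except the trial size.**
- 1000 patients per arm (2000 in total is stated; equal allocation is assumed).
- Other lower-extremity DVT b = 10% in both arms.
- True isolated distal DVT d = 3%, 5% or 10% in both arms, so IPC has no effect.
- Share of patients with a calf scan s = 10% in the IPC arm, against 15% (modest imbalance) or 30% (large imbalance) in controls.
- Being scanned is taken as independent of having a distal DVT.

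**Formulas.** Observed distal rate = d × s. All-DVT rate p = b + d × s. SE = √[p₁(1−p₁)/1000 + p₂(1−p₂)/1000]. Shift = (p₂ − p₁)/SE, where 1 is IPC and 2 is control. Two-sided error = P(|Z + shift| > 1.96), by normal approximation.

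| d | Imaged, IPC v control | Distal rates | Distal RR | All-DVT rates | All-DVT RR | Shift (SE) | Two-sided error |
|---|---|---|---|---|---|---|---|
| 3% | 10% v 15% | 0.30% v 0.45% | 0.67 | 10.30% v 10.45% | 0.986 | 0.11 | 5.1% |
| 5% | 10% v 15% | 0.50% v 0.75% | 0.67 | 10.50% v 10.75% | 0.977 | 0.18 | 5.4% |
| 10% | 10% v 15% | 1.0% v 1.5% | 0.67 | 11.0% v 11.5% | 0.957 | 0.35 | 6.4% |
| 3% | 10% v 30% | 0.30% v 0.90% | 0.33 | 10.3% v 10.9% | 0.945 | 0.44 | 7.2% |
| 5% | 10% v 30% | 0.50% v 1.50% | 0.33 | 10.5% v 11.5% | 0.913 | 0.71 | 11.0% |
| 10% | 10% v 30% | 1.0% v 3.0% | 0.33 | 11.0% v 13.0% | 0.846 | 1.38 | 28.0% |

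**Distal outcome.** In this model d cancels, and the RR is simply the ratio of imaging rates. At d = 5% the distal test favors IPC in about 11% of trials at 10% v 15% and in about 61% at 10% v 30%, against a nominal 2.5%. With as few as 5 v 7.5 expected events, the normal approximation is rough.

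**Other direction.** Swapping the arms inverts each RR. The distal RR becomes 1.5 or 3.0, and the all-DVT RR runs from 10.45/10.30 = 1.01 to 13.0/11.0 = 1.18. With equal imaging every RR is 1.00.

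**Lower base rate.** With b = 7%, the worst case (d = 10%, 10% v 30%) is 8% v 10%: RR 0.80, two-sided error about 35%.

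**Composite with mortality.** Assume 20% mortality independent of DVT, ignore PE, and count distal events. The case d = 5%, 10% v 30% gives 1 − 0.895 × 0.80 = 28.4% against 1 − 0.885 × 0.80 = 29.2%: RR 0.97, error 6.8%. At 15% to 30% mortality the error is 7.3% to 6.2%.

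**The case against.** Five points can be made for the plan.

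- **Nothing shows that imaging differs by arm.** This stands. A reader might infer that these RRs are already biased, or biased toward IPC. The documents support neither: bias needs an imbalance in calf imaging, and its direction is unknown.
- **The large figures need a large imbalance.** This also stands. At 10% v 15% the all-DVT error is close to nominal. In addition, clinically ordered scans select suspected cases, so the true distal RR need not equal the ratio of imaging rates.
- **The article already recognizes ascertainment bias.** It does, and comparing leg-scan counts is a partial check; a large excess of team-ordered scans could show up there. But the counts pool scheduled and clinical scans, do not isolate calf imaging, and correct nothing. The listed sensitivity analyses concern timing, survival and ICU stay, missing baseline scans and IPC duration; none removes distal-only events.
- **PE is also clinically ascertained.** True, so a proximal-only DVT component reduces the problem in the composites without removing it.
- **The outcomes are already published, and 1620 of 2000 patients had been enrolled by January 2018.** This is a fair argument against redefining them. It does not weigh against adding prespecified versions while the authors remain blinded to results.

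A reader might also take distal events to be part of the mortality composite. The wording allows that but does not say it.

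**Conclusion.** The point holds as a weakness in how these secondary outcomes are defined and compared. It is not evidence of actual bias. The distal RR cannot be interpreted without calf-imaging rates by arm. For all-DVT the distortion is near nil at a modest imbalance and moderate only at a large one. The DVT-plus-PE composite should behave much like all-DVT, and the composite with mortality should be affected least. Every size given rests on assumed distal DVT and imaging rates and on no IPC effect.

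A reader might extend this to the primary result. The primary outcome counts only incident proximal DVT, so distal events do not enter it as events. The inconsistency between setting isolated distal DVT aside and listing it as an outcome needs no assumption: it is in the text.

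**What to change.** 1. Report clinically diagnosed isolated distal DVT by arm as counts, beside the number of patients with team-ordered or calf-vein imaging, with no test and no RR.
2. Keep the published outcomes, and add a prespecified version of all lower-extremity DVT and of both VTE composites in which the DVT component is proximal DVT, incident plus prevalent. State that interpretation rests on this version where the two differ.
3. Reconcile the sentence that sets isolated distal DVT aside with the listed distal outcome, and say whether distal events count in the composite with 28-day mortality.

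The cost is a few more secondary analyses and a count of clinical or calf scans by arm. The documents do not say whether calf imaging is recorded separately; if it is not, team-ordered leg scans are the fallback. PE remains clinically ascertained in the composites.

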***Secondary outcomes related to PE***

*Incidence of PE*

*Extent of PE: unilateral, bilateral*
*PE with cardiopulmonary complications* (supraventricular arrhythmias, ventricular arrhythmias, hypotension (systolic blood pressure ≤ 80 mmHg or decrease of 30 mmHg from baseline) or increase in inotropic support ≥ 50% from pre-event, endotracheal intubation, cardiopulmonary arrest, pulmonary artery hypertension (pulmonary artery (PA) systolic ≥ 60 mmHg or death)
*Composite all lower-extremity DVT and PE*
4.
***Non-lower-extremity thrombosis***
5.***Lower-extremity skin pressure ulcers.*** This is a safety outcome, testing whether IPC increases the risk of skin pressure ulcers defined according to the National Pressure Ulcer Advisory Panel (NPUAP) classification6.***Lower-extremity ischemia.*** This is a safety outcome, testing whether IPC increases the risk of ischemia in the lower extremities by compromising blood flow7.***Serious adverse events (SAEs)*** defined in the study protocol as skin pressure ulcers of categories III and IV or ischemia due to IPC [5]8.***Non-tolerance to IPC*** defined as not using IPC for one calendar day or more because of discomfort9.Mechanical ventilation duration and mechanical-ventilation-free days, vasopressor therapy duration and vasopressor-free days, ICU stay and ICU-free days and hospital length of stay (LOS)10.

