**Methods/design:**

In this multicenter randomized trial, critically ill patients receiving pharmacologic thromboprophylaxis will be randomized to an IPC or a no IPC (control) group. The primary outcome is “incident” proximal lower-extremity deep vein thrombosis (DVT) within 28 days after randomization. Radiologists interpreting the lower-extremity ultrasonography will be blinded to intervention allocation, whereas the patients and treating team will be unblinded. The trial has 80% power to detect a 3% absolute risk reduction in the rate of proximal DVT from 7% to 4%.

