## Methods/design

### Study design

The PREVENT trial will enroll 2000 critically ill patients from 16 hospitals in 4 countries. The study has been approved by the Institutional Review Boards (IRBs) of the participating sites. The trial is registered at ClinicalTrials.gov: (NCT02040103) and Current Controlled Trials (ISRCTN44653506). The study is sponsored by King Abdulaziz City for Science and Technology (Grant number AT 65-34) and King Abdullah International Medical Research Center (Protocol number RC12/045/R), Riyadh, Saudi Arabia. The sponsors have no role in the study design, management or analysis.

All patients will be screened for eligibility within 48 h of ICU admission. Medical-surgical-trauma ICU patients, using accepted age cut-offs in participating adult ICUs (e.g. ≥ 14, 16 or 18 years), who weigh ≥ 45 kg, are expected to stay in ICU for ≥ 72 h and are eligible for pharmacologic thromboprophylaxis with either UFH and LMWH will be enrolled (Fig. 1). Exclusion criteria have been detailed in the protocol manuscript [5]. To enhance the generalizability of our findings, we permit the use of a broad array of IPC devices from various manufacturers intended for DVT prophylaxis. These devices include sequential devices (multi-chamber cuffs) and non-sequential devices (single-chamber cuff); the type of device will be recorded. IPC will be applied continuously for at least 18 h per day. The study intervention will continue for the duration of the ICU stay or up to 28 days after randomization; after which IPC use will be at the discretion of treating team. All enrolled patients will have a bilateral lower-extremity ultrasonography performed by a certified technologist at baseline (within 48 h of enrollment) and twice weekly thereafter until the diagnosis of a lower-extremity DVT or PE, ICU discharge, death, full mobility or 28 days (Fig. 2).

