### Intervention data

For each group we will report details regarding IPC use and the average daily duration of use (excluding study first and last days because they are usually less than 24 h, Additional file 1: Table S2). We will report reasons for not using IPCs in the IPC group and reasons for IPC use in the control group. We will classify these events as per-protocol and not per-protocol. We will classify IPC devices as sequential or non-sequential and will report the use of thigh- or knee-length sleeves and the use of foot pumps.

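### Non-tolerance to IPC, and at least the ischemia part of the SAE outcome, depend on IPC exposure, yet both outcomes go to a between-arm chi-square test and RR

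*Protocol article*

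**What the plan says.** All references are to the protocol article, which sets out the trial's statistical analysis plan.

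- **Secondary outcomes, item 7.** SAEs are "defined in the study protocol as skin pressure ulcers of categories III and IV or ischemia due to IPC".
- **Secondary outcomes, item 8.** Non-tolerance is "defined as not using IPC for one calendar day or more because of discomfort".
- **Secondary outcomes, items 5 and 6.** Lower-extremity ulcers and lower-extremity ischemia are separate safety outcomes. Item 5 is described as "testing whether IPC increases the risk of skin pressure ulcers defined according to the National Pressure Ulcer Advisory Panel (NPUAP) classification". Neither item requires attribution to the device.
- **Analysis of secondary outcomes.** "Secondary outcomes will be compared in the intention-to-treat cohort only using a chi-square test", and "Results will be reported using RR and 95% CI". The secondary-outcomes row of Table 1 repeats this. Neither place makes an exception for items 7 and 8.
- **Abstract, Methods/design.** Patients "will be randomized to an IPC or a no IPC (control) group".
- **Intervention data.** The report will give "reasons for IPC use in the control group", so some control exposure is expected. No rate is stated.

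**The concern.** A between-arm RR is informative only if a patient in either arm can have the event and it is counted by the same rule in both. Stopping a device for discomfort presupposes being on it, and ischemia caused by the device presupposes wearing it. In a control arm managed as allocated, neither event can be recorded.

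For non-tolerance, the comparison mostly restates who was given IPC. For SAEs, an ischemic limb in the IPC arm counts if it is judged to be caused by the device, while the same limb in a control patient without IPC does not count. The background frequency in controls, which is what randomization supplies, is then not used. A reader of the results table could take a large RR or a small p value on the SAE line as evidence of device harm when it partly reflects the definition.

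**Working it through.** **The plan's own figure.** The article gives no expected rate for either outcome. Its only design figure is 2000 patients for 80% power, 7% versus 4% proximal DVT. The two-proportion normal formula with continuity correction, two-sided with 1:1 allocation assumed, gives 971 per arm (1942 in total) at alpha 0.05 and 983 per arm (1966) at 0.048. That agrees with 2000. The present point does not depend on it, except that 1000 per arm is used below.

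**Step 1: who can have the event.**

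| Outcome | IPC arm | Control, managed as allocated | Control, off-allocation IPC |
|---|---|---|---|
| Non-tolerance (item 8) | possible | not possible | possible |
| SAE, ischemia component (item 7) | possible | not possible | possible |
| SAE, category III-IV ulcer, if the causal phrase governs ischemia only | possible | possible | possible |
| SAE, category III-IV ulcer, if it governs both | possible | not possible | possible |
| Any lower-extremity ulcer or ischemia (items 5, 6) | possible | possible | possible |

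The grammar of item 7 allows either reading of the ulcer component.

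**Step 2: non-tolerance.** Let q be the risk of non-tolerance among users, and c the share of control patients who use IPC. Assume that all IPC-arm patients use it and that q is the same for users in both arms.

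- IPC-arm risk = q; control risk = c × q
- RR = q / (c × q) = 1 / c

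The RR does not contain q. For assumed c of 2%, 5% and 10% it is 1/0.02 = 50, 1/0.05 = 20 and 1/0.10 = 10. With c = 0 it cannot be computed. With assumed q from 1% to 5% and 1000 per arm, expected control counts run from 1000 × 0.02 × 0.01 = 0.2 to 1000 × 0.10 × 0.05 = 5. The IPC arm would have 1000 × 0.01 = 10 to 1000 × 0.05 = 50.

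**Step 3: SAEs when IPC has no effect.** Let u be the risk of a category III-IV ulcer and r the risk of ischemia, equal in both arms. Let a be the share of events in IPC users that is attributed to IPC. Ignore overlap between components.

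- Causal phrase governs ischemia only: RR = (u + a × r) / (u + c × a × r). This exceeds 1 whenever a > 0, r > 0 and c < 1.
- Causal phrase governs both: RR = a(u + r) / [c × a(u + r)] = 1 / c, as in step 2.

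Under the first reading the bias is diluted by ulcers counted in both arms; under the second it is not. With perfect attribution and no device effect, a = 0 and the bias disappears. The comparison is therefore only as good as the causal judgement.

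**Step 4: how few one-sided events reach p < 0.05.** For x events versus 0 with n per arm, the uncorrected chi-square is 2n × x / (2n − x). With n = 1000:

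- x = 3: 6000 / 1997 = 3.00, p = 0.083
- x = 4: 8000 / 1996 = 4.01, p = 0.045

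With the Yates correction or Fisher's exact test it takes 6 events (p = 0.041 and p = 0.031). This is a property of the test against an empty control cell. It does not forecast the number of events.

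**The case against.** The strongest reply is that the main harm question is already handled. Items 5 and 6 are labelled safety outcomes and can be compared between arms with no causal judgement. This stands, and it limits the consequence. For ischemia, the attribution-free comparison already exists. What it leaves is a severity-specific ulcer comparison, since item 5 as written here does not single out categories III-IV, and an SAE line that will be reported and read as a harm comparison.

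It can also be said that the chi-square rule is shorthand, because the secondary list includes durations and serial scores for which the general Statistical analysis section names other methods. That is true, but items 7 and 8 are yes/no outcomes and fall squarely under the rule.

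Several stronger readings are tempting and are not supported:

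- **That control patients cannot have these events by construction.** The Intervention data section foresees IPC use in controls, and intention to treat keeps those patients in the control arm. The count is near zero, not zero by definition.
- **That severe ulcers have no attribution-free comparison.** This holds only if the causal phrase governs ulcers as well. The text does not settle that, and the detailed definitions are placed in Table S4 and the published protocol, which are not shown.
- **That an unblinded team makes the attribution.** The Abstract says that the treating team is unblinded. The article does not say who judges causality.
- **That a particular false harm signal is to be expected.** This needs background rates and an attribution share that the article does not give.
- **That the one-day threshold for non-tolerance conflicts with Study design**, where "IPC will be applied continuously for at least 18 h per day". One is an application target and the other an outcome definition. Partial use still appears in the planned report of average daily duration. A count of days below the target would be an added measure, not a correction.

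**Conclusion.** The point holds in limited form. Non-tolerance, and at least the ischemia component of the SAE outcome, depend on exposure to IPC, while the plan applies a between-arm intention-to-treat chi-square test and RR to them. For non-tolerance the RR has a near-zero denominator and mainly reflects allocation: about 10 to 50 for an assumed 10% to 2% control use, and not estimable with none. For SAEs the RR is biased by one-sided attribution, for the ischemia component alone or for the whole outcome. The size of the SAE bias cannot be given from the article.

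The illustration assumes 1:1 allocation with 1000 per arm, full IPC use in the IPC arm and equal non-tolerance among users in both arms. The qualitative conclusion needs only that control use of IPC is much rarer than use in the IPC arm. The primary outcome is untouched, and items 5 and 6 remain valid safety comparisons.

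**What to change.** 1. **SAE comparison.** For the between-arm analysis, count category III-IV lower-extremity pressure ulcers and lower-extremity ischemia by the same rule in both arms, whatever the suspected cause. Keep the chi-square test and RR for that outcome.
2. **Attributed events.** List events attributed to IPC descriptively by arm, without a test, and state whether the causal phrase in item 7 covers ischemia only or ulcers as well.
3. **Non-tolerance.** Take it out of the chi-square and RR comparison in Analysis of secondary outcomes and Table 1. Report it in the IPC arm as a proportion with 95% CI. Any occurrence in off-allocation control users can go in the table of control-group IPC use.

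The cost is a change of wording before database lock. Ulcers by NPUAP classification, ischemia and reasons for not using IPC are already to be reported. The sponsor should confirm that ulcer category is recorded in the control arm as well. The change concerns the analysis outcome only and leaves SAE reporting during the trial as it is.
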